### 5.2.2 Exclusion Criteria

- Currently participating in an interventional clinical trial in which any treatment or follow-up is mandated
- Women with a contraindication for prescription of REKOVELLE® treatment
  - Hypersensitivity to the active substance or to any of the excipients
  - Tumours of the hypothalamus or pituitary gland
  - Ovarian enlargement or ovarian cyst not due to polycystic ovarian syndrome
  - Gynaecological haemorrhages of unknown aetiology
  - Ovarian, uterine, or mammary carcinoma
  - Primary ovarian failure
  - Malformations of sexual organs incompatible with pregnancy
  - Fibroid tumours of the uterus incompatible with pregnancy
  - Pregnancy and breast feeding
- Women who undergo ovarian stimulation for fertility preservation
- Women placed under judicial protection, guardianship, or supervision
- Women who are considered as vulnerable population.

### 5.3 Trial Withdrawal/Treatment Discontinuation Criteria

Participation in this trial is voluntary and women are free to withdraw from the trial at any time and for any reason without prejudice to their drug prescriptions or therapeutic management. Missing routine care visits at one or more time points or missing questionnaires will not be considered as criteria for Subject withdrawal.

If a woman withdraws from the trial, regardless of cause, the date and the reason for trial withdrawal will be documented in the e-CRF, if this information is available. Subjects who withdraw from the trial will be informed that data collected up to that point will be used in the trial analyses but that after withdrawal no further data will be collected for them.

### 5.4 Site Selection

This trial will be conducted in Nordic Countries (Sweden, Denmark, Norway) and Switzerland in Europe, at 15 sites known to treat and follow-up subjects undergoing COS and routinely prescribe REKOVELLE®. Fifteen IVF centres will be activated for the trial.

This trial will be proposed to public hospitals and private clinics, spread evenly across the territory, with the capacity to perform this observational trial and that use the ELECSYS AMH Plus Immunoassay from Roche or ACCESS AMH Advanced from Beckman Coulter or LUMIPULSE G AMH from Fujirebio to measure woman's serum AMH concentration.

## 5.5 Duration of Trial

The total duration of the trial will be approximately 24 months (from first subject first visit to data base lock). The duration of treatment is per investigators' judgement.

| Trial Milestone                                      | Estimated Date |
|------------------------------------------------------|----------------|
| Ethics submission                                    | Q2 2022        |
| Site Initiation visits                               | Q3 2022        |
| Start of data collection (first subject first visit) | Q3 2022        |
| Last subject inclusion                               | Q4 2023        |
| End of data collection (last subject last visit)     | Q1 2024        |
| Data base lock                                       | Q1 2024        |
| Final Trial Report                                   | Q2 2024        |

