## **STATISTICAL METHODS**

### **Statistical analysis**

This is a descriptive trial. There are no hypotheses to be tested and no inferential statistics will be applied. All descriptions of data will be based on all subjects enrolled in the trial who meet the inclusion/exclusion criteria and who receive at least one dose of REKOVELLE®. Therefore, pregnancy rates will be calculated for all subjects starting stimulation with REKOVELLE®, and mean number of oocytes, embryos, blastocysts etc. will be the mean for all subjects starting stimulation with REKOVELLE®.

Missing data for pregnancy outcomes will be regarded as “no pregnancy”. Missing data for number of oocytes, number of embryos, number of blastocysts, and similar endpoints will be regarded as zero.

The primary endpoint, real-life treatment patterns in first cycle with REKOVELLE® will be extensively described.

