| rFSH               | recombinant Follicle Stimulating Hormone                                                                                                                            |
| SADR               | Serious Adverse Drug Reactions                                                                                                                                      |
| SAP                | Statistical Analysis Plan                                                                                                                                           |
| WHO                | World Health Organization                                                                                                                                           |
| Total Trial Period | Total trial duration time for the trial (approximately 2 years from First Patient First Visit (FPFV) to Last Patient Last Visit (LPLV).                             |
| Enrolment period   | Period in which a given site may enrol new subjects (after the completion of the subject consent process) and may capture data for subject's 1st REKOVELLE® cycles) |

|                                                             |                                                                                                                                                                                                                                                                                                                                                                                              |
|-------------------------------------------------------------|----------------------------------------------------------------------------------------------------------------------------------------------------------------------------------------------------------------------------------------------------------------------------------------------------------------------------------------------------------------------------------------------|
| Observation period                                          | 
For a subject:
 
 
From informed consent through 1st cycle with REKOVELLE®;
 
In case of pregnancy, up to 11 weeks gestation (pregnancy follow-up)
 
 
For a site:
         Enrolment period+ subject observation period (through ongoing cycle and pregnancy follow-up if applicable)
                                    |

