### 4 METHODS

#### 4.1 Trial Design

This is a European trial including Nordic Countries (Sweden, Denmark, Norway) and Switzerland. A Prospective, multi-centre, post-authorisation, non-interventional observational cohort trial conducted in routine clinical practice under real-life conditions in fertility clinics to

collect information from 200 naïve women treated with REKOVELLE® and undergoing IVF or ICSI procedures.

As the trial is non-interventional, the decision to treat subjects with REKOVELLE® will be independent from the decision to enrol the subject into the trial. Subjects will be enrolled only after the treatment decision has been made and no aspect of this trial will interfere with or influence the routine medical procedures and/or medications received. No trial medications will be provided.

In each site, during the enrolment period, consecutive women who are prescribed REKOVELLE® for IVF/ICSI cycle according to the approved label, will be invited to participate in the trial. The trial enrolment will be monitored, and the enrolment will be locked once 200 women initiated with REKOVELLE® have been enrolled. Each woman will contribute only for one stimulation cycle over the observation period.

During the observation period, the investigators will collect data for one stimulation cycle with REKOVELLE® or until early withdrawal. Data about transfer cycles using frozen embryos/blastocysts will be collected only for the first transfer cycle if they are performed within 3 months after the cycle stimulated with REKOVELLE® within the observation period.

Women with embryo/blastocyst transfer will be followed until the ongoing pregnancy (approximately 10-11 weeks after the first fresh or frozen transfer) or no pregnancy is confirmed or early pregnancy loss or trial withdrawal. Ultrasound results must be obtained if not performed at the participating site.

Baseline, COS treatment and follow-up assessments will be performed by the investigators during routine local clinical care visits.

Subject questionnaire will be completed by the subjects at the clinic after cycle cancellation, trial withdrawal or before the oocyte retrieval.

At the enrolment visit and for each eligible woman, the investigator will:

- Explain the trial to the woman, in particular, the objective of the trial and its epidemiological nature
- Give her the Informed Consent Form (ICF) and ask the subject to read and sign it to confirm her agreement to participate

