#### **13.3 End of Trial**

The total duration of the trial will be approximately 24 months (from Ethics Submission to Database Lock). Last subject out will correspond to the last ongoing pregnancy (10-11 weeks after the embryo/blastocyst transfer) among the women included during the enrolment period.

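### Milestones with last inclusion in Q4 2023 and database lock in Q1 2024 do not fit a 3-month frozen-transfer window plus 10-11 weeks, and two wordings of that window conflict

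*Protocol*

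**What the plan says.** **Dates.** The same milestone table stands in the Protocol Outline (Planned Trial Period) and in section 5.5. "Last subject inclusion" is Q4 2023. "End of data collection (last subject last visit") is Q1 2024, and so is database lock. First subject first visit is Q3 2022 and ethics submission Q2 2022. The dates are labelled as estimates.

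**Follow-up.** Section 4.1 follows women with a transfer "until the ongoing pregnancy (approximately 10-11 weeks after the first fresh or frozen transfer"). Section 13.3 ends the trial to match: "Last subject out will correspond to the last ongoing pregnancy (10-11 weeks after the embryo/blastocyst transfer") among the women included.

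**Frozen-transfer window.** There are two versions. The Outline (Methodology), section 4.1 and the footnotes to Table 1 collect the first frozen transfer if it is made within 3 months of the stimulated cycle and inside the observation period. The Outline (Duration of Participation) and the follow-up entry in the list of definitions keep the 3 months but require the transfer to fall inside the enrolment period.

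**Scoring.** The Outline (Statistical analysis) uses all women starting stimulation as denominator and adds: "Missing data for pregnancy outcomes will be regarded as" no pregnancy.

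**Duration.** Section 5.5 states: "The total duration of the trial will be approximately 24 months (from first subject first visit to data base lock"). The list of definitions has "approximately 2 years from First Patient First Visit (FPFV) to Last Patient Last Visit (LPLV"). The Outline counts from ethics submission to last visit, and section 13.3 from ethics submission to lock.

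**The concern.** One secondary endpoint is ongoing pregnancy following the fresh cycle and including the first frozen transfer. Its longest path is stimulation, retrieval, up to 3 months to the transfer, then 10-11 weeks. That path is longer than the time between most Q4 2023 inclusion dates and the end of Q1 2024. A woman under a freeze-all strategy has no fresh transfer, so a frozen one is her only route to this endpoint.

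Because the denominator is all starters and a missing outcome is a failure, a result that has not yet happened at lock, or that a rule leaves uncollected, lowers the rate. It is then reported as treatment outcome when it is an effect of the calendar.

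**Working it through.** **1. The plan's own figure: 24 months.** Take the earliest and latest day of each quarter.
- First visit to lock: 30 Sep 2022 to 1 Jan 2024 = 15.0 months; 1 Jul 2022 to 31 Mar 2024 = 21.0 months. The 24 months of section 5.5 is not reproduced. First to last visit, the anchor in the definitions, gives the same 15-21 months.
- Ethics submission to last visit or lock: 30 Jun 2022 to 1 Jan 2024 = 18.1 months; 1 Apr 2022 to 31 Mar 2024 = 24.0 months. This reaches 24 only at its extreme.
- Counting 24 months from first visit would put lock in July to September 2024, which would accommodate the follow-up.

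**2. Inputs for the follow-up path.** The 3 months and the 10-11 weeks (70-77 days) are from section 4.1. Assumptions: 9-12 days of stimulation (the answer options in the subject questionnaire; the protocol fixes no length), 2 days to retrieval, and stimulation starting on the day of consent. The last is the most favourable case for the plan.

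**3. Completion date** = inclusion + 11 to 14 days + 3 months + 70 to 77 days, for a transfer at the 3-month limit:

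| Included | Retrieval | Window closes | Endpoint |
|---|---|---|---|
| 1 Oct 2023 | 12-15 Oct | 12-15 Jan 2024 | 22 Mar-1 Apr 2024 |
| 15 Nov 2023 | 26-29 Nov | 26-29 Feb 2024 | 6-16 May 2024 |
| 31 Dec 2023 | 11-14 Jan 2024 | 11-14 Apr 2024 | 20-30 Jun 2024 |

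For the last woman, the transfer window itself closes after the latest possible lock.

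**4. Latest inclusion that fits 31 Mar 2024.**
- With 10 weeks: 31 Mar - 70 days = 21 Jan 2024; - 3 months = 21 Oct 2023; - 11 to 14 days = 7-10 Oct.
- With 11 weeks: 14 Jan 2024; 14 Oct 2023; 30 Sep-3 Oct.

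**5. Fresh transfers.** Assume transfer 2-5 days after retrieval. A 31 Dec inclusion ends 23 Mar to 5 Apr 2024. The slowest path is 12 + 2 + 5 + 77 = 96 days, so inclusion by 26 Dec still finishes by 31 Mar.

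**6. The enrolment-period wording.** The last admissible frozen transfer is 31 Dec 2023; adding 70-77 days gives 10-17 Mar 2024, which fits. But a full 3-month window then needs retrieval by 30 Sep 2023, so inclusion by 16-19 Sep. Women included after 17-20 Dec have retrieval after enrolment closes and no window at all.

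**7. Scale (illustration only).** With uniform accrual of 200 women to 31 Dec 2023, starting between 1 Jul and 30 Sep 2022, the number included after the cut-off in step 4 is:
- 200 x 82/548 = 30 (cut-off 10 Oct, start 1 Jul), to
- 200 x 92/457 = 40 (cut-off 30 Sep, start 30 Sep).

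Each ongoing pregnancy missed lowers the rate by 1/200 = 0.5 percentage points. Suppose 30-60% of these women have a first frozen transfer, 60% of those transfers come too late for lock, and 25-35% of them lead to ongoing pregnancy. None of these rates is in the protocol. Then 30 x 0.30 x 0.60 x 0.25 = 1.35 to 40 x 0.60 x 0.60 x 0.35 = 5.04 pregnancies are missed, or 0.7 to 2.5 points.

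**The case against.** Four objections carry weight.

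- **The dates are estimates.** Section 13.3 defines the end by the last ongoing pregnancy, and no text orders lock while women are still in follow-up. If the sponsor follows 13.3, the dates slip and nothing is lost. This stands: the bias is conditional. But the entries span whole quarters, and the conflict remains on the last day of Q1 2024.
- **The enrolment-period wording makes the dates fit.** True. It contradicts section 4.1, however, and it moves the loss from an early lock to a rule that shortens the window for late enrollees while they stay in the denominator.
- **Three months is a maximum, and enrolment is competitive.** A retrieval on 15 November with a frozen transfer on 15 December ends about 1 March 2024. Enrolment locks at 200 women, which could be reached in early October. Both limit how many women are affected.
- **The trial is descriptive and the primary endpoint, treatment patterns, is untouched.** This stands and sets the severity.

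A reader might infer that every woman included in Q4 2023 will be scored a failure, that the fresh-cycle rate is also distorted, or that the bias is a known number of points. The documents support none of these. Early-October inclusions and early frozen transfers can finish. The fresh-cycle rate is touched only for inclusions in the last days of December on the slowest path. The size needs accrual, transfer and pregnancy rates that the protocol does not give.

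**Conclusion.** The point holds as an internal contradiction. Under the observation-period wording, the Q1 2024 last visit and lock cannot accommodate a frozen transfer at the 3-month limit for women included after about 30 September to 10 October 2023. Under the enrolment-period wording the dates fit, but the window is not the same for every woman. If lock falls on the listed dates, or the enrolment-period wording is applied, the missing-data rule pushes the ongoing-pregnancy rate including the first frozen transfer downward.

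The direction is firm; the size is not. The completion dates rest on 9-12 stimulation days, 2 days to retrieval and stimulation starting at consent; any delay after consent moves the cut-off earlier. Separately, the 24 months in section 5.5 disagrees with the table beneath it, and the protocol anchors that duration in four ways.

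This should be fixed. It concerns mainly one secondary descriptive rate and leaves the primary endpoint unaffected.

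**What to change.** 1. Reconcile the enrolment-period and observation-period wordings for frozen transfers, so that every woman has the same window. Do this before the dates are set, because the dates depend on it.
2. Then either set last visit and lock after last inclusion + stimulation + 3 months + 11 weeks (about end of June or early July 2024 for a Q4 2023 last inclusion), or keep lock in Q1 2024 and close inclusion by about the end of September 2023, earlier if stimulation does not start at consent.
3. State one duration with one start and one end point, consistent with the table and with section 13.3.
4. Do not apply the no-pregnancy rule to women whose follow-up window is still open at lock. Report their number, and define the group by inclusion or retrieval date, not by whether an outcome is known, since negative results become known sooner than ongoing pregnancies.

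Cost: a few lines of protocol text, and either lock and report about one quarter later or recruitment closing about one quarter earlier.

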## 6 ASSESSMENTS

Due to the observational nature of the trial, all assessments will be performed per routine clinical practice.

### 6.1 Schedule of Assessments

Only data available in subject's records and needed to fulfil the trial objectives will be collected.

Visits will be done in accordance with routine clinical practice.

The flowchart of data collected by the investigators is provided in Table 1.

**Table 1 Trial Flowchart**

| Data                                                                                                                                                                                         | Baseline data | COS Cycle data @ | Follow-up data \$ |
|----------------------------------------------------------------------------------------------------------------------------------------------------------------------------------------------|---------------|-----------------------------|------------------------------|
| Data Collected by the Investigators                                                                                                                                                   |               |                             |                              |
| Informed consent §                                                                                                                                                                | X             |                             |                              |
| Inclusion/exclusion criteria                                                                                                                                                                 | X             |                             |                              |
| Socio-demographic data                                                                                                                                                                       | X             |                             |                              |
| Infertility / menstrual / reproductive history                                                                                                                                               | X             |                             |                              |
| Antral follicle count if available                                                                                                                                                           |               |                             | X                            |
| Most recent AMH measurement (within the last 12 months) performed with ELECSYS AMH Plus Immunoassay from Roche or ACCESS AMH Advanced from Beckman Coulter or LUMIPULSE G AMH from Fujirebio | X             |                             |                              |

| Data                                                                                                 | Baseline data | COS Cycle data@ | Follow-up data\$ |
|-------------------------------------------------------------------------------------------------------------|----------------------|-----------------------------------|------------------------------------|
| Other laboratory measurements, as available (FSH, LH, estradiol, progesterone, TSH, prolactin as available) | X                    |                                   |                                    |
| Results from imaging techniques, as available                                                               | X                    |                                   |                                    |
| Results of most recent pelvic ultrasound as available                                                       | X                    |                                   | X                                  |
| REKOVELLE® dosing regimen prescribed, number of days of treatment & , dose changes           |                      | X                                 |                                    |
| Usage of algorithm                                                                                          |                      | X                                 |                                    |
| Usage of dosing App                                                                                         |                      | X                                 |                                    |
| Gonadotropin dosing regimen: initial dose prescribed                                                        |                      | X                                 |                                    |
| Ovarian stimulation protocol used                                                                           |                      | X                                 |                                    |
| Stimulation day, Triggering of final follicular maturation                                                  |                      | X                                 |                                    |
| Monitoring of the REKOVELLE® treatment (number and intents of each visit)                                   |                      | X                                 |                                    |
| Luteal support drugs used                                                                                   |                      |                                   | X                                  |
| Number of oocytes retrieved                                                                                 |                      |                                   | X                                  |
| Number of frozen oocytes/embryos/blastocysts                                                                |                      |                                   | X                                  |
| Number of embryos/blastocytes transferred                                                                   |                      |                                   | X                                  |
| Quality of fresh/frozen embryos/blastocysts transferred                                                     |                      |                                   | X                                  |
| Pregnancy outcomes +                                                                             |                      |                                   | X                                  |
| Pregnancy loss                                                                                              |                      |                                   | X                                  |
| Cycle cancelled and reason for cycle cancellation                                                           |                      | X                                 | X                                  |
| ADRs serious and non-serious                                                                                | X                    | X                                 | X                                  |
| Fatal events, related and non-related                                                                       | X                    | X                                 | X                                  |
| OHSS (mild/moderate/severe)                                                                                 |                      |                                   | X                                  |
| Preventive measures for OHSS                                                                                |                      |                                   | X                                  |
| Trial termination form                                                                                      |                      |                                   | X                                  |
| Medical history and concomitant treatment*                                                                  | X                    | X                                 | X                                  |
| Data collected by the Subjects                                                                       |                      |                                   |                                    |
| Subject Questionnaire #                                                                          |                      | X                                 |                                    |

@Data to collect until oocyte retrieval or early withdrawal.

\$ Data to collect after oocyte retrieval, including transfer cycle or early withdrawal.

& REKOVELLE® treatment gathers all the treatment procedures related to the stimulation preparation and the stimulation period up to the triggering of the final follicular maturation.

§ Written informed consent must be obtained prior to any Trial related data collection.

+ Ultrasound results must be obtained if not performed at the participating site. Data about cycles using frozen embryos/blastocysts will be collected only for the first transfer cycle if they are performed within 3 months after the cycle stimulated with REKOVELLE® within the observation period.

+ Pregnancy outcomes described with Positive signs of pregnancy (hCG test or urine pregnancy test) and clinical pregnancy (at least one gestational sac 5-6 weeks after transfer)

\* Concomitant medication will be collected for all ADRs, both concomitant medication and medical history will be collected for all serious ADRs and fatal AEs.

# Subject questionnaire will be completed by the subjects at the clinic after cycle cancellation or before oocyte retrieval.

